### Covariates

The following covariates will be evaluated to determine their effects on the outcomes.

#### Participant characteristics

Participant characteristics will be evaluated using a questionnaire authorized by the Japan Prosthodontic Society [29, 30]. We will collect data on the participants’ intraoral condition-associated characteristics, i.e., on the residual ridge morphology, oral mucosa condition, maxillomandibular relationship, abnormal habits, saliva quantity and quality, and frenum attachment. In addition, data will be collected on various denture-associated characteristics, i.e., on the denture base material, artificial teeth material, denture condition, pain, retention, history of denture use, and whether the patients wear their dentures at night. Furthermore, data on the participants’ sociodemographic, medical, and anthropometric (weight, height) characteristics will be collected. The participant characteristics will be measured at baseline.

#### Oral dryness

The objective oral dryness will be measured using an oral moisture-checking device (Mucus, Life Co., Saitama, Japan). The device can measure the oral mucosal moisture level within 2 s with 200 mg of pressure. The measurements will be performed by placing a sensor vertically onto the oral mucosa until the surface of the sensor and mucosa are attached firmly. The measurement area is the lingual mucosa located 10 mm from the apex linguae [31, 32]. The oral dryness that will be used as one of the inclusion criteria will be measured at day 0 and day 4.

### Statistical analysis

First, analyses of normality using the Kolmogorov–Smirnov test will be performed for all variables. When normality can be verified, parametric tests will be performed. However, if normality cannot be verified, then two types of analyses will be performed, as follows: (1) the distributions of the dependent variables will be normalized by the appropriate transformations for parametric tests, or (2) nonparametric tests will be performed.

The between-subjects comparisons among the three groups will be performed using one-way analyses of variance with Tukey-Kramer post hoc tests or Kruskal-Wallis tests with Mann-Whitney *U* tests adjusted with the Bonferroni correction. The within-subjects comparisons of the pre- and post-intervention measurements will be performed by either paired *t* tests or Wilcoxon signed-rank tests. Furthermore, the multiple regression analysis will be performed using the abovementioned covariates as predictors.

Subgroup analyses will also be undertaken among the different subpopulations defined by each of the multiple baseline characteristics of the participants in order to study whether the effects of the intervention vary across these patient characteristics.

All of the analyses will be performed in accordance with the intention-to-treat principle, and various strategies to account for any post-randomization missing data will be contemplated. However, in the sensitivity analyses, we will also perform per protocol analyses to assess the robustness of our findings with regard to potential incomplete adherence; in particular, patients with major protocol violations or poor adherence will be excluded.

All statistical analyses will be performed using the IBM SPSS Statistics Package v21 (IBM, Armonk, NY, USA). A *p* value of <0.05 will be considered statistically significant.

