### Sample size calculation

A between-group difference of 29 mm on the visual analog scale (VAS) ratings for general satisfaction was considered a meaningful difference. By using variances of 20 mm in the intervention groups and 23 mm in the control group, which were based on previously reported data [22, 23], 100 subjects per group, including an assumed dropout rate of 10 %, will be required to achieve 80 % power with an alpha level of 5 %.

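### The test and effect scale for the primary outcome hang on a normality test with two unranked fallbacks, so neither is fixed before the data are seen

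*Protocol article*

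**What the plan says.** All of the rule is in the Statistical analysis section of the protocol article.

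- First step: "analyses of normality using the Kolmogorov–Smirnov test will be performed for all variables". No exception is made for the primary outcome.
- If the test is passed: "When normality can be verified, parametric tests will be performed".
- If it is failed: "if normality cannot be verified, then two types of analyses will be performed, as follows". The two are then given as (1) "the distributions of the dependent variables will be normalized by the appropriate transformations for parametric tests, or (2) nonparametric tests will be performed".
- The tests themselves are also written as alternatives: between groups, "one-way analyses of variance with Tukey-Kramer post hoc tests or Kruskal-Wallis tests" (the latter followed by Bonferroni-adjusted Mann-Whitney tests); within groups, "either paired *t* tests or Wilcoxon signed-rank tests".

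The Sample size calculation section sets the benchmark on the raw scale: a between-group difference of 29 mm on the VAS "ratings for general satisfaction was considered a meaningful difference". Under Primary outcome measures, general satisfaction is a single 0–100 mm rating read to 1 mm, at baseline and day 4.

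**The concern.** Three things that should be settled in advance are open.

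1. **Raw scale or fallback** is decided by a significance test on the trial's own data.
2. **Which fallback** has no rule at all. The sentence announces two analyses and then joins them with *or*, so it is unclear whether both are run or one, and which would count if they differ. No transformation is named.
3. **How the normality test is run** is not stated: per arm, pooled or on residuals, and with or without correction for estimated mean and SD.

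The three routes estimate different things: a mean difference in mm, a difference on a transformed scale, or a rank comparison. Only the first is directly on the scale of the 29 mm benchmark. The trial is meant to support clinical guidelines, so readers need to know beforehand which quantity is the primary result.

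**Working it through.** **Inputs from the article.** 100 per group with 10% dropout gives 100 × 0.90 = 90 evaluable. Spread is 20 mm (intervention) and 23 mm (control); these are called variances but are in mm, so they are read as SDs. The pooled SD is √((20² + 23²)/2) = √464.5 = 21.55 mm. Alpha is 5% (two-sided assumed), power 80%, meaningful difference 29 mm.

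**Assumptions not in the article.** It gives no expected VAS mean or shape. The simulations use normal scores rounded to 1 mm and clipped to 0–100, with means of 50 to 80 mm.

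**Step 1. The plan's own sample size.** n = (20² + 23²)(1.960 + 0.842)²/29² = 929 × 7.849/841 = 8.67, so 9 per group, or 10 with dropout. This does not reproduce 100. That is a separate matter; 90 evaluable per arm is taken as given here.

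**Step 2. Is the gate needed?** The standard error of a difference in means is 21.55 × √(2/90) = 3.21 mm. A 29 mm difference is 29/3.21 = 9.0 standard errors, giving power above 99.9%. The difference detectable with 80% power is 3.21 × 2.802 = 9.0 mm. In the null simulations below, ANOVA on the clipped raw scores, with no gate, rejected in 4.5–5.6% of trials, so comparing means at this size does not rely on passing a normality test.

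**Step 3. How often does the gate send the trial to a fallback?** No treatment effect, 90 per arm, SD 21.5, 4,000 runs; Kolmogorov–Smirnov test corrected for estimated parameters (Lilliefors), run in each arm, with failure in any arm triggering the fallback.

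| Mean VAS | To fallback | Type I error: preset Kruskal-Wallis | Type I error: preset transformation (square) | Type I error: best fallback picked afterwards |
|---|---|---|---|---|
| 50 | 12.3% | 5.3% | 5.3% | 5.9% |
| 60 | 14.2% | 4.6% | 4.4% | 5.0% |
| 70 | 31.3% | 5.0% | 5.0% | 6.1% |
| 80 | 99.8% | 5.1% | 5.2% | 7.6% |

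The last column takes the smallest p-value among Kruskal-Wallis and three transformations, only when the gate has failed. Simulation error at 5% is √(0.05 × 0.95/4000) = 0.34 points. Three 5% tests on exactly normal data would fail at least once in 1 − 0.95³ = 14.3% of trials, so the first two rows are essentially the test's own false alarms. The ceiling drives the last two.

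**Step 4. Does the unstated method of testing matter?** Take a mean of 70 mm, SD about 22, no effect.

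- Corrected, per arm: 14% of arms fail, so 1 − 0.86³ = 36% of trials (31% in the run above at SD 21.5).
- Corrected, all 270 pooled: about 87% of trials.
- Uncorrected, per arm: 0.2% of arms, so 1 − 0.998³ = 0.6% of trials. At a mean of 80 mm it is 14% of arms, so 1 − 0.86³ = 36% of trials.

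The same data could go to the raw scale or to a fallback depending on a choice the article leaves open.

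**The case against.** The strongest defence is that the numerical damage is small and depends on inputs the article does not give. That stands. With one preset fallback the error rate is nominal. At the plan's own 29 mm effect every route would be significant, so the conclusion on significance would not change. An uncorrected test would rarely trigger the fallback unless scores sit near the ceiling.

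Some stronger readings are tempting but not supported:

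- *A treatment effect alone makes the pooled VAS fail, and 29 mm guarantees it.* Pooling is not stated. An unclipped mixture with a 29 mm shift was rejected in only about 19–34% of trials across repeated runs. With clipping the figure ran from about 18% to 100% according to the assumed control mean. The ceiling does most of the work.
- *Three p-values are available at once, giving about 8% false positives.* Under the stated rule, raw and fallback analyses are alternatives. A figure near 8% for the smallest of three p-values ignores the gate and is not the plan's error rate.
- *A rank result could not be set against 29 mm.* Raw means in mm can be reported beside a rank test, and nothing in the article forbids it. What is missing is a commitment on which result is primary.

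It may also be said that an unseen analysis plan settles this. But the article is not silent: it states a rule, and that rule is ambiguous as written.

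**Conclusion.** The point holds as a defect in a stated rule. The gate makes the route depend on the data, and after failure the choice between an unnamed transformation and rank tests is left to the analyst. The main harm is an unfixed estimand and discretion after seeing the data; error inflation is secondary. Under the assumed clipped-normal scores, the per-arm corrected test diverts about 12% to nearly 100% of trials as the mean goes from 50 to 80 mm. Type I error is about 4.4–5.3% with a preset fallback and about 5–8% if the better one is picked after the results are seen. These figures rest on an assumed VAS mean and shape, on reading 20 and 23 mm as SDs, and on the transformations tried. The ambiguity in the text rests on none of them. It should be corrected, and correction is cheap.

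**What to change.** In the Statistical analysis section:

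- Remove the normality gate for general satisfaction.
- Name one primary between-group comparison of mean VAS in raw mm, preferably adjusted for the baseline VAS already collected, with robust or bootstrap confidence intervals. Baseline adjustment is an improvement; naming one raw-scale analysis is what cures the defect.
- Report Kruskal-Wallis and Mann-Whitney results only as a sensitivity analysis that cannot replace the primary one.
- If a transformed analysis is kept, name the transformation and give it the same sensitivity status.

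The change should be dated, with a statement of whether any interim comparison by group had been seen, because looks are planned after 100 and 200 participants.

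The cost is one reworded paragraph and no new data. The downside is a possible small loss of efficiency if the VAS is very skewed; with 90 per arm and 29 mm as the target, the plan can afford it.

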While a few clinical trials have been published in Japan, they were not RCTs. Moreover, the results derived from Japanese denture wearers might be different from those mentioned in previous studies performed in other countries since patients’ attitudes toward dental materials reflect food culture and socioeconomic differences among the countries. Therefore, guidelines or official statements concerning the use of denture adhesives in clinical practice in Japan cannot be developed at this time. Performing RCTs and collecting data that can be used to develop clinical practice guidelines to standardize the usage, raise the quality of care, and reduce the risk for older Japanese individuals is essential, since there are many older individuals in Japan who cannot receive denture treatment in a dental clinic owing to their physical conditions, meaning they may turn to dental adhesives instead. Thus, we plan to perform an RCT at the following ten centers: Iwate Medical University, Tohoku University, Tokyo Medical and Dental University, Nihon University School of Dentistry at Matsudo, Tsurumi University, Kanagawa Dental College, Osaka Dental University, Tokushima University, Nagasaki University, and Kagoshima University. This ten-center RCT, which will be performed throughout Japan, has external validity. This trial is referred to as the Denture Adhesive Guideline (DAG) project. The aim of the DAG trial is to verify the efficacy of denture adhesives in order to establish guidelines for using denture adhesives in clinical practice in Japan. The null hypothesis of this study is that the application of two types of denture adhesives (cream and powder) and a control would not produce differences in the set outcomes and would not result in differences in the improvement of the set outcomes between baseline and day 4 following application.

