### Primary outcome measures

Experts and members of the Japan Denture Care Society selected the outcomes for the current trial after reviewing previously published articles on denture adhesives. The primary outcome is a general satisfaction rating obtained with a 100-mm VAS. The satisfaction ratings will be determined using valid questionnaires with eight evaluation items: general satisfaction, ability to speak, ease of cleaning, stability, retention, comfort, and esthetics [24]. The participants will be asked to assess their current existing complete dentures and to record their satisfaction rating for each item on the questionnaire by drawing a vertical line on a 100-mm VAS. Each vertical line in the questionnaire represents “very satisfied” (100) at the extreme right and “very dissatisfied” (0) at the extreme left. Data will be recorded as continuous variables at 1-mm intervals using calipers, beginning at the extreme left. The general satisfaction will be measured twice: at baseline and day 4.

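### The three-group ANOVA has no baseline term and an unnamed response, so it is valid but less precise than ANCOVA; the paired tests have no stated role and cannot test the null

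*Protocol article*

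**What the plan says.** The Statistical analysis section of the protocol article sets out three analyses.

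- **Between groups:** "The between-subjects comparisons among the three groups will be performed using one-way analyses of variance with Tukey-Kramer post hoc tests". If normality fails and no transformation is used, Kruskal-Wallis with Bonferroni-adjusted Mann-Whitney tests replaces it. Group is the only factor in either branch. The section does not say whether the response is the day-4 score or the change from baseline.
- **Within arms:** "The within-subjects comparisons of the pre- and post-intervention measurements will be performed by either paired" t tests or Wilcoxon signed-rank tests.
- **Regression:** "the multiple regression analysis will be performed using the abovementioned covariates as predictors". The Covariates section, which opens "The following covariates will be evaluated to determine their effects on the outcomes", then lists participant characteristics and oral dryness. The baseline satisfaction score and centre are not on that list.

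On the primary outcome the article says: "The general satisfaction will be measured twice: at baseline and day 4". The null hypothesis in the Background compares the two adhesives with the control, and its second half is that they "would not result in differences in the improvement of the set outcomes between baseline and day 4 following application". A single threshold of p<0.05 is given for all analyses.

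**The concern.** The baseline value of the primary outcome is collected, and it is usually the best single predictor of the day-4 value. The named between-group test has no term for it. The regression, as listed, does not bring it in either. Information already paid for therefore goes unused, or is used inefficiently if the response is change.

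The paired tests raise a different problem. Both halves of the null hypothesis compare groups, and a paired test inside one arm compares nothing across groups. Participants cannot be blinded and rate their own satisfaction, so expectation and regression to the mean can move the score in any arm, including the saline arm. With no role assigned to these tests, a report that an adhesive arm improved significantly and the control arm did not could be taken as evidence of efficacy. The trial is meant to support national guidelines, so the basis for the efficacy conclusion should be fixed in advance.

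**Working it through.** **Inputs from the Sample size calculation section:** 29 mm meaningful difference; 20 mm and 23 mm, printed as variances but usable only as SDs; 100 per group including 10% dropout, hence 90 evaluable; alpha 5%, power 80%.

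**Assumptions, because the article gives no figure:** baseline/day-4 correlation r of 0.3, 0.5 or 0.7; equal SD at both times; two-sided tests. The article does not say whether 20/23 mm describe day-4 scores or changes, so both readings are shown.

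**The plan's own figure.** Pooled SD = √((20² + 23²)/2) = 21.55 mm. For 29 mm, n = 2 × 464.5 × (1.960 + 0.842)² / 29² = 8.7, so 9 per group, or 10 with dropout. The stated 100 is not reproduced. That is a separate matter and nothing below depends on it, but at 90 per arm the power for 29 mm exceeds 99.99% under any of these analyses.

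**Variance of ANCOVA relative to the alternatives.**

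| r | against day-4 ANOVA, 1 − r² | against change ANOVA, (1 − r²)/(2(1 − r)) = (1 + r)/2 |
|---|---|---|
| 0.3 | 0.91 (9% lower) | 0.65 (35% lower) |
| 0.5 | 0.75 (25% lower) | 0.75 (25% lower) |
| 0.7 | 0.51 (51% lower) | 0.85 (15% lower) |

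**Detectable difference, Tukey-adjusted, 80% power, 90 per arm.** SE of a pairwise difference = 21.55 × √(2/90) = 3.21 mm. The Tukey critical value for three groups on 267 degrees of freedom, on the t scale, is 3.333/√2 = 2.357. Detectable difference = (2.357 + 0.842) × 3.21 = 10.3 mm.

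- If 20/23 mm are day-4 SDs, ANCOVA gives 10.28 × √(1 − r²) = 9.8, 8.9 and 7.3 mm for r = 0.3, 0.5 and 0.7.
- If they are change SDs, ANCOVA gives 10.28 × √((1 + r)/2) = 8.3, 8.9 and 9.5 mm.

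**Control arm's paired test.** Suppose a non-specific shift of 5 mm, day-4 SD 21.55 mm and n = 90. Change SD = 21.55 × √(2(1 − r)). Probability of significance ≈ Φ(5/(change SD/√90) − 1.96).

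| r | change SD (mm) | SE (mm) | probability |
|---|---|---|---|
| 0.3 | 25.5 | 2.69 | 46% |
| 0.5 | 21.6 | 2.27 | 60% |
| 0.7 | 16.7 | 1.76 | 81% |

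**Disagreement between arms when all improve equally.** If each arm's paired test has power p, the three do not all agree with probability 1 − p³ − (1 − p)³: 48% at p = 0.8 and 75% at p = 0.5. In a simulation of 20,000 trials (90 per arm, r = 0.5, the same true improvement of 3, 4.5 or 6 mm in every arm), at least one adhesive arm was significant while control was not in 24% to 37% of trials. The between-arm ANOVA of day-4 scores rejected in 4.8% to 5.1%.

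**Centre.** At 9 mm, where an unadjusted two-group comparison with 90 per arm has 80% power, adjusting for centre gives 80.4%, 82.0% and 84.0% for assumed between-centre variance shares of 0.01, 0.05 and 0.10.

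**The case against.** The best defence is that the named test is sound and that the missing details may sit in a fuller document. Much of this stands, and it rules out four stronger readings that a reader might infer.

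- **That the ANOVA ignores baseline.** The response is not named. If it is change, which would suit the improvement half of the null, baseline enters by subtraction. Change scores are still less precise than ANCOVA at any r below 1.
- **That the result would be invalid.** Allocation is not stratified by centre, and the unadjusted ANOVA keeps its error rate, as the simulation shows. Its standard error already allows, on average, for chance baseline imbalance. The cost is precision.
- **That omitting centre is a serious fault.** The gain from adding it is small over the assumed range.
- **That paired tests decide efficacy.** The article never says so. It lists the between-group comparison first and labels the others as within-subject. The weakness is only that they have no stated role. ANCOVA would not remove expectation effects either, because those also enter between-arm contrasts in a trial with unblinded participants.

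It is also fair to say that the regression sentence is not a full model specification, since it does not name treatment arm either, and that at a true difference of 29 mm the extra precision would not change the result. What the objection does not remove is that the article names a specific test with no covariate, has the baseline score in hand, and sets paired tests beside the between-group test at the same threshold.

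**Conclusion.** The point holds as a matter of efficiency and clarity; it does not show an invalid analysis. The named comparison is valid but less precise than a baseline-adjusted one, by 9% to 51% of the variance if the response is the day-4 score and by 15% to 35% if it is change, for assumed correlations of 0.3 to 0.7. The detectable difference falls from 10.3 mm to between 7.3 and 9.8 mm, or to between 8.3 and 9.5 mm, depending on what the 20/23 mm figures describe. All of these lie well below 29 mm, so the gain would show mainly in narrower intervals, in the comparison of cream with powder, and in any effect smaller than planned.

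The paired tests cannot test either half of the null. The 46% to 81% chance of a significant control-arm result rests on an assumed 5 mm shift and a day-4 SD of 21.55 mm.

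**What to change.** In the Statistical analysis section:

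1. Make the primary analysis an ANCOVA of day-4 general satisfaction on arm and baseline general satisfaction, and report Tukey-Kramer adjusted pairwise differences in mm with 95% CIs. Centre may be added, for a smaller gain.
2. Use the same model for secondary outcomes measured at both times.
3. If normality fails, use a baseline-adjusted alternative such as rank ANCOVA in place of Kruskal-Wallis and Mann-Whitney tests.
4. Label the paired tests descriptive, and state that efficacy conclusions rest on the between-arm contrasts.

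The cost is a change of wording. The baseline scores are already collected, so no new data and no additional participants are needed. The change should be made before any comparison by arm is seen, bearing in mind that interim analyses are planned at 100 and 200 completed participants.

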### Randomization, allocation concealment, and sequence generation

A randomized, controlled parallel clinical trial will be conducted at the abovementioned ten centers. Participants will be randomly assigned to one of the following three groups and will be instructed to apply either a denture adhesive or a control solution to both their maxillary and mandibular dentures: cream-type denture adhesive group, powder-type denture adhesive group, and control group (Fig. 1). Balanced allocation of participants to each group will be achieved using the following method: 300 random allocation numbers with no overlap and no underlap will be generated by the “RAND” and “RANK” functions in Excel (Microsoft Japan Co. Ltd., Tokyo, Japan). The first to 300^th^ numbers will be ordered randomly. Then, the first to 100^th^, 101^st^ to 200^th^, and 201^st^ to 300^th^ randomly ordered numbers will be assigned to the cream-type denture adhesive group, powder-type denture adhesive group, and control group, respectively. As per the assignment, 300 envelopes containing a card stamped with the group name will be prepared. The 300 envelopes will be divided 30 by 30 for ten centers in sequence, which means that each of the ten centers will receive 30 envelopes. Then, the coordinator at each center will open one envelope and allocate a qualifying participant to the indicated group after the patient agrees to participate in the study and provides informed consent. This method enables us to allocate the 300 numbers to the three groups equally and randomly. Once the 300 participants have been completely allocated, the number of participants in each of the three groups will be equal. Blinding the participants to the intervention is not feasible, since the participants will be able to determine the type of denture adhesive they are using during application. Evaluators are blinded to the allocation.

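### Single-step Bonferroni on the three Mann-Whitney comparisons is valid but needlessly conservative; Holm step-down gives the same family-wise protection and more power for cream versus powder

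*Protocol article*

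**What the plan says.** The Statistical analysis section fixes two routes for comparing the three groups, chosen by a normality check: "one-way analyses of variance with Tukey-Kramer post hoc tests or Kruskal-Wallis tests". On the second route the pairs are compared by Mann-Whitney "tests adjusted with the Bonferroni correction". Neither sentence says that pairs are examined only if the three-group test is significant.

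There are exactly three arms: "cream-type denture adhesive group, powder-type denture adhesive group, and control group (Fig. 1"). The null hypothesis in the Background covers all three: "the application of two types of denture adhesives (cream and powder) and a control would not produce differences in the set outcomes". Cream versus powder is therefore one of the planned comparisons.

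The Sample size calculation states one meaningful difference without naming the pair: "A between-group difference of 29 mm on the visual analog scale (VAS) ratings for general satisfaction was considered a meaningful difference". It gives "variances of 20 mm in the intervention groups and 23 mm in the control group", a dropout rate of 10% and 100 subjects per group. It gives no separate difference for cream versus powder.

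**The concern.** Bonferroni tests every pair as if all three null hypotheses could still be true, even after one or two have been rejected. If both adhesives are clearly better than control, only cream versus powder remains open, yet that pair is still held to 0.0167. A step-down method relaxes the threshold as hypotheses are rejected, at no cost in family-wise error.

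The trial is meant to support guidance on two product types, so the pair that loses power is one of its stated questions. The loss can affect any outcome, primary or secondary, that is analysed by the nonparametric route.

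**Working it through.** **Inputs.** From the protocol article: three arms, 100 per group, 10% dropout (100 × 0.9 = 90 evaluable), 29 mm, spreads of 20 and 23 mm, alpha 5%, power 80%. Assumptions: two-sided tests; the spreads are SDs (they are called variances, but the unit is mm); normal data; true cream-versus-powder differences of 6 and 8 mm.

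**The plan's own figure.** The average variance is (20² + 23²)/2 = 464.5, so n = 2 × (1.960 + 0.842)² × 464.5 / 29² = 8.7. That is 9 per group, or 10 after dropout. The stated 100 does not reproduce from these inputs. That discrepancy is a separate matter; here only the 90 evaluable per arm is carried forward.

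**Thresholds.**
- Bonferroni: each pair at 0.05/3 = 0.0167, z = 2.394.
- Holm: smallest p at 0.05/3 = 0.0167, next at 0.05/2 = 0.025, last at 0.05 (z = 1.960), stopping at the first failure.
- Shaffer, three groups: 0.0167, then 0.05 and 0.05, because once one pair differs at most one pairwise null can be true.

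No Holm or Shaffer threshold is below 0.0167, so every pair that Bonferroni rejects is also rejected by the step-down method. This is true whether or not the Kruskal-Wallis test acts as a gate, since a gate would apply equally to both.

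**Adhesive versus control at 29 mm.** Standard error = √((20² + 23²)/90) = 3.21 mm and 29/3.21 = 9.0. Both comparisons with control are rejected almost surely, so Holm then tests cream versus powder at 5%.

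**Cream versus powder.** Standard error = 20 × √(2/90) = 2.98 mm. The large-sample efficiency factor of the Mann-Whitney test for normal data is √(3/π) = 0.977.

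| True difference | Standardised effect | Bonferroni power | Holm power |
|---|---|---|---|
| 6 mm | 0.977 × 6/2.98 = 1.97 | Φ(1.97 − 2.394) = 33% | Φ(1.97 − 1.960) = 50% |
| 8 mm | 0.977 × 8/2.98 = 2.62 | Φ(2.62 − 2.394) = 59% | Φ(2.62 − 1.960) = 75% |
| 29 mm | 0.977 × 29/2.98 = 9.5 | about 100% | about 100% |

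Simulation agrees: about 32% against 48–50% at 6 mm, and about 58% against 74% at 8 mm.

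**Error spent.** With cream equal to powder and both 29 mm above control, simulated Bonferroni Mann-Whitney error is about 1.7% of the allowed 5%. Holm tests that pair at its full nominal 5%, which is what the family-wise guarantee permits.

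**ANOVA route, for the optional part.** On 267 degrees of freedom the critical |t| is 2.357 for Tukey and 1.969 unadjusted. At 8 mm (SDs 20/20/23, adhesives about 29 mm above control) power is 58% with Tukey. With pairs tested at 5% only after a significant omnibus test, it is 73% with a pooled error term and 76% with unpooled pairwise tests. When one adhesive equals control and the other is superior, the gated rule with pooled error has a family-wise error of about 5.5–5.6%; unpooled pairwise tests bring it to 5.0%. Without the gate, unadjusted tests give about 12%.

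**The case against.** The strongest objection is that nothing here is wrong. Tukey-Kramer and Bonferroni both control the family-wise error, and at 29 mm, the only difference the protocol calls meaningful, every method has about 100% power. That stands, and it limits the point to efficiency.

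The size of the gain is also conditional. It needs both adhesives well above control. If control lies midway between them, cream versus powder is usually the smallest of the three p-values, and Holm tests that one at the same 0.0167. Even the gated rule on the ANOVA route then gains little (76% against 73% with means 9, 0 and 4.5 mm and SD 20 throughout). This stands too.

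A reader might go further and infer that the Tukey route is uniformly less powerful, because an omnibus test in a three-group trial already protects the pairs. The documents do not support that. The protocol never makes the Tukey tests conditional on a significant ANOVA, and Tukey used without a gate can reject when the omnibus test does not. With means 8, 0 and 4 mm that happens in about 1.7% of simulated trials. Tukey also has a legitimate advantage in that its simultaneous intervals match its tests. Under the gated rule at 8 mm, about 73 − 58 = 15 trials in 100 would declare a difference beside a Tukey interval that includes zero, roughly one in five of the significant results (15/73).

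Finally, the protocol plans interim analyses after 100 and 200 participants and states no adjusted level for them. The 5% guarantee above is for a single analysis, under Bonferroni and Holm alike; choosing between them does not resolve repeated looks.

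**Conclusion.** The point holds for the Bonferroni-adjusted Mann-Whitney comparisons: Holm dominates Bonferroni under the same family-wise guarantee, so the single-step penalty buys no additional error control. For cream versus powder the cost is about 16 to 18 percentage points of power at assumed true differences of 6 to 8 mm. This rests on 90 evaluable per arm, SDs of 20/20/23 mm, normal data and both adhesives about 29 mm or more above control. The cost is nil at 29 mm and small when control lies between the adhesives.

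It should not be read as showing that the planned analysis is invalid, or that Tukey-Kramer must be replaced. On the ANOVA route the choice is a trade between power and matching intervals, and reasonable statisticians may differ. Priority is low.

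**What to change.** In the Statistical analysis section, replace "tests adjusted with the Bonferroni correction" by: *tests adjusted with the Holm step-down procedure*. Shaffer's version is an acceptable alternative. Fix the wording before any between-group results are seen, which matters here because interim analyses are planned. The cost is one phrase: no extra patients or data, and Holm can be applied by hand to the three p-values.

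Optionally, on the ANOVA route, state that each pair is tested at 5% only if the three-group test is significant, and that otherwise no pair is declared different. The pairwise tests should be unpooled (Welch), because the planning SDs differ. The price is that test decisions would no longer match Tukey simultaneous intervals. If matching intervals are wanted, leave Tukey-Kramer as it is.
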